### Inclusion criteria

2.4

The criteria listed below are required for participation and enrollment in the study.•Age between 18 and 65 years (inclusive), of either sex•ICU admission for at least 24 h•Initiation of EN for a minimum of 24 h prior to enrollment•Hemodynamically stable at the time of inclusion•Receiving ≥60% of the prescribed protein requirements via EN (for various reasons, such as severe catabolism, adequate protein intake cannot be achieved via EN alone after 3-7 days, and approximately 60% of the total protein requirement is provided enterally, it is advisable to initiate supplemental parenteral nutrition (SPN) alongside enteral nutrition to provide protein and calorie intake to patients).•Provision of written informed consent by the patient's legal representative following full disclosure of the study objectives and procedures.

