### Randomization and allocation

2.7

Given the importance of randomization on the one hand and the need for balanced sample sizes between the studied groups on the other hand, the random permutation block method is used. For this purpose, random permutation blocks of length 4 with two interventions are generated, and patients are allocated to the intervention arms accordingly. Allocation will be concealed in sealed envelopes prepared by an independent researcher.

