### Blinding

2.8

Patients will be assigned to either an HP diet or a CP intake plan. We acknowledge that complete blinding in nutritional intervention trials may be challenging, particularly when individualized protein targets or supplemental parenteral nutrition are required. The nutritional formulations provided in both groups will be visually indistinguishable, share similar color, texture, and packaging, and will be delivered in identical containers labeled with unique codes. Protein dosing will be adjusted by an ICU-based clinical dietician unaffiliated with the research team to ensure healthcare personnel remain blinded. As a result, healthcare personnel, including medical and nursing staff, will be blinded to the nutritional content administered to each participant. Given patients’ critical illness and reduced consciousness, they are not aware of their treatment assignment, which inherently reduces the risk of patient-level bias. If supplemental parenteral nutrition is required, it will be documented and considered in the analysis to minimize bias. Outcome assessments, including serum zonulin measurements, clinical scoring systems such as SOFA scores, and mortality rates, will be assessed by blinded independent raters without knowledge of the groups to which the patients were allocated. APACHE II and mNUTRIC scores were assessed only at ICU admission. All the data will be coded and deidentified prior to statistical processing, and the biostatistician will remain blinded until the final analysis is completed.

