#### Intervention

2.10.3

The intervention group will receive HP enteral nutrition at a dosage of 1.6 g/kg/day, whereas the control group will receive CP enteral nutrition at a dosage of 1.2 g/kg/day. The intervention will last for 10 days in ICU-admitted patients.

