#### Confounding variables

2.10.6

Potential confounding variables include age, sex, BMI, APACHE II score at ICU admission, admission diagnosis category, vasopressor use during the intervention, and underlying comorbidities. Comorbidities will be categorized into predefined clinical groups, including Trauma, cancer, surgery, diabetes mellitus, kidney disease, cardiovascular disease, and liver disease. These factors should be measured and considered, as they may influence outcomes.

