#### Statistical analysis

2.10.16

The data will be analyzed via SPSS version 25. The normality of the data will be assessed with the Kolmogorov‒Smirnov test. Descriptive statistics will include the mean ± SD for normally distributed variables and the interquartile range (IQR) for nonnormally distributed variables. Pre- and postintervention measures will be compared using a paired *t*-test, whereas frequency tables and medians will describe categorical and continuous data. Categorical variables will be analyzed via the chi-square test or Fisher's exact test, and continuous variables will be analyzed via the Mann‒Whitney *U* test. Survival analysis (Kaplan‒Meier and Cox regression) will be used for time‒to‒event outcomes, and ANCOVA will compare primary outcomes at baseline, day 5, and day 10. Potential confounders including age, sex, BMI, APACHE II score at ICU admission, admission diagnosis category, vasopressor use during the intervention, and predefined comorbidity groups will be included as covariates in multivariable regression and ANCOVA models. These adjusted analyses will be applied to both primary (zonulin levels) and secondary outcomes where appropriate to minimize residual confounding. Longitudinal regression models will assess the intervention's effect, controlling for the same confounding factors. Statistical significance will be set at p < 0.05.

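### Vasopressor use after randomisation is treated as a confounder and adjusted for in the treatment-effect models, which can bias the adjusted estimates

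*Protocol article*

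**What the plan says.** Section 2.10.6 (Confounding variables) ends its list of potential confounders with "vasopressor use during the intervention, and underlying comorbidities". Section 2.10.16 (Statistical analysis) turns that list into a modelling rule: "vasopressor use during the intervention, and predefined comorbidity groups will be included as covariates in multivariable regression and ANCOVA models". The scope is wide: "These adjusted analyses will be applied to both primary (zonulin levels) and secondary outcomes where appropriate to minimize residual confounding". The longitudinal regression models then assess the intervention while "controlling for the same confounding factors".

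The other listed covariates are age, sex, BMI, APACHE II at ICU admission, admission diagnosis category and comorbidity groups. These describe the patient at or before entry. The vasopressor term alone is tied to the treatment period, and nothing in the article limits it to use at baseline.

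**The concern.** Allocation is random (section 2.7: "random permutation blocks of length 4 with two interventions are generated"). A confounder of a randomised comparison would have to influence which arm a patient receives, and something that happens after allocation cannot do that. Vasopressor use over the following ten days can only be a consequence of the arm, a marker of how ill the patient became, or both.

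Conditioning on such a variable can do two kinds of harm. If protein acts partly by changing haemodynamic course, the model holds that part of the effect fixed and so removes it. If unmeasured severity drives both vasopressor use and zonulin, patients with the same vasopressor status in the two arms no longer have the same severity on average, and a difference can appear that treatment did not cause. At stake is the adjusted estimate for the primary outcome and for any secondary outcome given the same covariates.

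**Working it through.** **Reading the article**

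1. Timing. The inclusion criteria (section 2.4) require patients to be "Hemodynamically stable at the time of inclusion". Vasopressor use in the treatment period is therefore determined largely after entry.
2. Path from arm to covariate. The arms differ in protein target (1.6 versus 1.2 g/kg/day, section 2.10.3). The secondary objective (2.10.2) is an effect on illness severity and mortality, and the Discussion expects protein intake to alter the course of disease. On the trial's own hypothesis, vasopressor need may lie downstream of the arm.
3. Order of measurement. Zonulin is sampled on days 0, 5 and 10. If the covariate is one summary over the whole period (its coding is not given), the day-5 comparison would be adjusted partly for events after the day-5 sample.

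**Size**

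The plan states no figure on this point, so there is none to reproduce. It gives a zonulin mean of 3.40 ng/mL, an SD of 0.71 and a target difference of 10%, which is 0.34 ng/mL (section 2.9). It gives no vasopressor rate and no association between vasopressors and zonulin. All other inputs below are assumptions.

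Model, with 1,000,000 simulated patients per scenario:

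- arm T = 0 or 1, randomised; severity U standard normal and unmeasured
- logit P(V = 1) = −0.4 + a·T + g·U, where V is vasopressor use
- zonulin Y = 3.40 + d·T + b·V + h·U + error, with h·U plus error having SD 0.71

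The unadjusted effect is the difference in mean Y between arms. The adjusted effect is the T coefficient from a linear model with T and V.

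| Scenario | a, g, h, b, d | V, control vs high protein | Unadjusted | Adjusted | Change |
|---|---|---|---|---|---|
| A. Arm does not affect V | 0, 1, 0.35, 0.2, −0.34 | 42% vs 42% | −0.338 | −0.338 | none |
| B. V is a mediator only | −0.6, 0, 0, 0.4, −0.25 | 40% vs 27% | −0.306 | −0.252 | 18% lost |
| C. True null, V shares severity with Y | −0.6, 1, 0.35, 0, 0 | 42% vs 30% | 0.000 | +0.033 | false difference |
| D. Both paths | −0.6, 1, 0.35, 0.4, −0.25 | 42% vs 30% | −0.296 | −0.217 | 27% lost |
| E. Both paths, stronger | −1, 1.5, 0.5, 0.4, −0.25 | 43% vs 27% | −0.314 | −0.163 | 48% lost |

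Loss = 1 − adjusted/unadjusted; for E, 1 − 0.163/0.314 = 0.48.

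Scenario B can be checked by hand. The total effect is d + b × (difference in V) = −0.25 + 0.4 × (0.269 − 0.402) = −0.303. The adjusted effect is d = −0.25. The loss is 0.053/0.303 = 18%.

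A lower rate of vasopressor use shrinks the loss but does not change the mechanism. In a similar simulation (severity coefficients 0.7 on V and 0.5 on zonulin, b = 0.5, d = −0.3), 15% use in the control arm with falls of 0, 2, 3.5 and 8 points gave losses of 0%, 6%, 12% and 24%. If high protein raised vasopressor use instead, the false difference in scenario C would change sign and favour high protein.

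**The case against.** The strongest reply is that no bias has been shown. It arises only if the assigned protein changes vasopressor use; the arms differ by 0.4 g/kg/day, and scenario A shows no bias otherwise. Patients with sepsis at screening are excluded and stability is required at entry, so rates near 42% are not an obvious central value. This stands: the size and direction are unknown, and the range must include zero. It does not rescue the covariate, which removes no confounding and is not needed to estimate the effect of assignment.

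Second, other comparisons are planned that do not use the covariates: chi-square or Fisher's exact tests, Kaplan–Meier curves and Mann–Whitney tests. The secondary outcomes are adjusted only where appropriate, and no model is named as decisive for mortality. A reader might infer that the mortality conclusion rests on the affected models; the article does not say so. For zonulin, however, ANCOVA is the named analysis.

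Third, a reader might extend the point to supplemental parenteral nutrition, since section 2.8 says "If supplemental parenteral nutrition is required, it will be documented and considered in the analysis to minimize bias". That is in no covariate list, and being considered could mean a description by arm or a sensitivity analysis. No such adjustment is stated, so none can be criticised.

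Fourth, a reader might say that the SOFA model adjusts for part of its own outcome. Section 2.10.13 names the cardiovascular system but does not say how it is scored. The overlap follows only on the assumption that vasopressors enter that score.

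**Conclusion.** The point holds in conditional form. Sections 2.10.6 and 2.10.16 fix a post-randomisation variable as a covariate in the ANCOVA, multivariable and longitudinal models for zonulin and, where appropriate, the secondary outcomes. It cannot reduce confounding between randomised arms, and it can bias the adjusted estimate if the assigned protein affects vasopressor use. Under the assumed values the loss of effect runs from none to about half, and a false difference of about 0.03 ng/mL can appear when there is no effect. These figures illustrate the mechanism and do not predict what this trial will see. The stronger statement, that the adjusted effect is biased, is not supported, because the article reports neither vasopressor rates nor any effect of protein on them.

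**What to change.** In sections 2.10.6 and 2.10.16, delete the vasopressor term or replace it with vasopressor use before randomisation. Deletion may be simpler, because the stability criterion may leave little variation at baseline. State that the treatment-effect models for the primary and secondary outcomes use pre-randomisation covariates only. Report vasopressor use in the treatment period by arm, or use it only in an analysis labelled as supplementary.

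The cost is a change of wording, and the article says recruitment had not begun. Medication during the intervention is already to be recorded by drug class (section 2.1), so the report by arm needs no new data. A baseline version would require confirming that use before randomisation is captured. The models lose whatever outcome variance the deleted term would have explained, a small price for an estimate that keeps the protection of randomisation.

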## Discussion

3

This study is the first clinical trial that examined the effects of high-protein enteral nutrition on intestinal permeability, disease severity, and mortality in critically ill patients in the ICU. Critically ill ICU-admitted patients are often at risk of sepsis, inflammation, and impaired intestinal barrier function [25]. These patients are also prone to malnutrition and systemic inflammation, which lead to poor outcomes and increased mortality rates [26].

Nutritional support, especially enteral nutrition and protein intake, can effectively improve epithelial barrier function and reduce intestinal permeability in these patients [16].

Zonulin is a membrane protein that plays a role in maintaining tight junctions between intestinal epithelial cells (through binding to proteins such as claudin, occludin, junctional adhesion molecules, and the actin cytoskeleton) and is considered a marker of epithelial barrier function [27]. The production of this protein is usually regulated by inflammatory cytokines such as IL-1, IL-6, and TNF-α and is increased during inflammatory conditions [28].

The gastrointestinal microbiome can also influence the clinical status of critically ill patients [29]. Dysbiosis or an imbalance in the microbiome is associated with increased zonulin secretion, impaired intestinal permeability, and inappropriate regulation of inflammatory mediators [30]. Therefore, enteral nutrition and protein intake can significantly affect the disease process, epithelial barrier function, and intestinal permeability [16].

The SOFA score is a suitable tool for predicting survival and ICU discharge [31,32]. The APACHE II score also estimates the severity of the disease on the basis of data from the first 24 h of hospitalization [33]. The mNUTRIC questionnaire is also used as a screening tool for the risk of severe malnutrition in ICU patients [34,35].

The present study aims to identify a scientific gap by investigating the effects of high protein administration in enteral nutrition on serum zonulin concentrations, severity of illness scores (APACHE II, SOFA), nutritional risk, and mortality in ICU patients. If protein administration causes a significant reduction in zonulin levels and improved clinical outcomes, the results of this trial could influence future guidelines on protein dosing in enteral nutrition in ICU patients [13].

These findings support the implementation of personalized nutritional strategies aimed at optimizing not only the energy supply but also gut health and systemic status in critical care settings [36,37]. Future studies could also examine the impact of protein on the gastrointestinal microbiome and inflammatory markers to better elucidate the broader immunoinflammatory role of nutrition in the gut‒brain axis in critically ill patients.

## Trial registration

This trial was registered on December 11, 2024 in the Iranian Registry of Clinical Trials (ID: IRCT20241129063891N1). This document represents the first version of the study protocol, finalized in Decmber 2025. Participant recruitment has not yet commenced and is anticipated to begin within the next month. The estimated duration for data collection is approximately 12 months.

## Ethics approval and consent to participate

The study protocol followed the SPIRIT checklist. This trial was approved on 2024-11-17 with the ethics code of IR. MUMS.REC.1403.298 at Mashhad University of Medical Sciences. It is also registered with the Iranian Clinical Trials Registry (IRCT20241129063891N1). This trial will be performed in accordance with the Declaration of Helsinki. We will obtain informed consent from the patient's legal guardian, and the study objectives and procedures will be fully explained, with an emphasis on confidentiality and voluntary participation. The results will be published without mentioning the names or characteristics of the study participants. All patients benefit from their standard routine treatment, and no treatment is removed from the patients' routine care.

## Data Availability

No data was used for the research described in the article.
